### MRI

Regarding MR, we shall use a 3D sequence using a Toshiba TITAN 3T MRI (Canon Medical Systems, Corporation in Nasu, Japan), with a phase 3D MPV Voxel mVox T2 weight, isotropic Voxel (0.6 mm, 90.6 mm and 90.6 mm).

With a T2 FAT SAT sequence (fat saturation) in the sagittal plane, the dimensions of the intra-tendinous changes will be measured using several signal characteristics: hypo-signal, homogeneous signal, heterogeneous signal, isointense signal, and normal signal. Proximal, medial and distal areas of altered signal will be measured in millimetres. Hoffa fat oedema and patellar bone oedema will also be evaluated. An FFE (Fast FE) 3D sequence will be used in the coronal plane to measure the gap and the gap in cross-section diameter in millimetres. The presence of calcification will also be assessed. UTE (Ultrashort Echo TE) sequences will be obtained in the sagittal plane, and T2 mapping will be acquired in regions of Interest (ROI), and will be established for the areas of altered signal, in the medial and lateral areas, and in healthy tendon.

The intra-articular appearance of the knee joint will also be assessed, with quantification of the degree of arthrosis (I–IV) of each knee compartment.

### Criteria for non-response to treatment

A lack of response to treatment will be recorded if no clinically relevant improvement or tendon repair changes occur after a 6-month period. Clinical changes will be assessed using a combination of physical examination, VAS score, VISA-P questionnaire and DYN. Tendon repair will be assessed using ultrasonography, UTC and MRI. A partial response will be considered if there is evidence of either clinical improvement or tendon repair.

### Patient and public involvement

Patients and the public were not directly involved with the development of the current protocol. The primary research question is the efficacy of the use of culture-expanded MSCs versus LP-PRP on the treatment of patellar tendinopathy. This will enable the development of a larger RCT that will involve oversight from the patient and public representatives. Patient recruitment is described above, and the results will be disseminated to the participants directly in the doctor's office at the end of the study.

### Statistical analysis

Statistical analysis will be performed using version 21. 0 of the Statistical Package for Social Sciences (SPSS Inc, Chicago, IL). We will evaluate: (i) adverse events (AE) and serious adverse events (SAE) showing relationships, causality and severity will be provided; (ii) frequency and percentage of AE and SAE; (iii) laboratory results including hematologic and biochemistry values will be collated: leukocytes levels, absolute neutrophils count, platelet count, creatinine levels, AST (SGOT)/ALT (SGTP) levels, etc. A list of laboratory parameters will be obtained for each patient and visit and will include reference range values. Values will be summarized in a basal and post-basal visit analysis will include the following values: (i) valid ‘n’; (ii) mean; (iii) standard deviation; (iv) median; (v) minimum and maximum.

The frequency and percentage values of patients showing evidence of tendon regeneration 6 months after treatment with MSC or P-PRP will be provided.

The following methods will be used to describe and analyse the results obtained:
Descriptive statistics in numerical variables: number of valid cases; number of non-available values; mean value; standard deviation; 95% confidence interval for the mean value; median, minimum and maximum values. In discrete and categorical variables, the following values will be provided: frequency; percentage value for the total number of valid cases; percentage value for the total number of non-available values.Inferential statistics tests for comparing groups and time points: ANOVA with repeated measures (or ANCOVA) if covariables with a significant interaction are detected with their corresponding contrast values (Scheffe test), or non-parametric tests if the assumption of normality is rejected (Mann-Whitney *U* test for comparison between groups and Wilcoxon test for comparison between measurements). The significance level for all statistical analyses will be 0. 05.

Efficiency sample (per protocol (PP) population) includes all patients whose tendon lesion has been treated with an MSC or LP-PRP suspension. These patients must have had no major violations of the protocol, and at least one assessment of efficacy after treatment.

‘Full analysis set’ (FAS) (intention to treat analysis) includes all patients in the study, whether they finish the study or comply with the protocol.

The safety population will be used in the analysis of the primary endpoint and of all other safety parameters defined.

A list of all demographic and baseline data will be provided for each patient. All lists will be provided for FAS and PP populations.

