**Methods and analysis:**

This is a single-centre, pilot phase I/II, double-blinded clinical trial with randomisation with active control. Twenty patients with a diagnosis of patellar tendinopathy with imaging changes (tendon thickening and disruption of the intratendinous substance at the proximal portion of the patellar tendon) will be randomised in a 1:1 ratio to receive a local injection of either bone-marrow autologous mesenchymal stem cells (MSC), isolated and cultured under GMP at T*he Institute of Biology and Molecular Genetics* (IBGM) (Spain) or P-PRP. The study will have two aims: first, to ascertain whether a clinically relevant improvement after 3, 6 and 12 months according to the visual analogue scale (VAS), Victorian Institute of Sport Assessment for patellar tendons (VISA-P) and dynamometry scales (DYN) will be achieved; and second, to ascertain whether the proposed intervention will restore tendon structure as determined by ultrasonography (US), Doppler ultrasonography (DUS), and innovative MRI and ultrasound techniques: Magnetic Resonance T2 FAT SAT (UTE, Ultrashort Echo TE) sequence and Ultrasound Tissue Characterization (UTC). Patients who are randomised to the P-PRP treatment group but do not achieve a satisfactory primary endpoint after 6 months will be offered treatment with MSC.

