## Methods/design

### Main objectives

To assess the clinical efficacy of MSC injection and compare the results with those obtained in the LP-PRP group. Outcomes will be assessed using subjective patient reports, VAS and VISA-P scales, and strength determination of the extensor muscle group using manual dynamometry (DYN).To confirm changes in the architecture for regeneration of the patellar tendon gap following peritendinous and intratendinous injection of MSC and compare these results with those obtained in the LP-PRP group. Assessment will be performed using UTE-MRI, UTC and ultrasonography.

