### Response evaluation

Subsequent assessments following the treatment include AE review, VAS (pain), VISA-P Questionnaire, ultrasound imaging (conventional ultrasound, UTC and MRI), dynamometry manual test and clinical assessment (Table 2 for phase A, and Table 3 for phase B). These will take place at 1, 2, 3, 6, 8 and 10 weeks and 3, 6, 12 months post-treatment.

**Table 2 Tab2:** Outcome assessments experimental phase A

Study period															
	Enrollment				Treatment		Follow-up								
Timepoints					0	23 days	1 week	2 weeks	3 weeks	6 weeks	8 weeks	10 weeks	3 months	6 months	12 months
Inf. sheet	X														
Incl/excl Criteria		X													
IC		X													
Preop + serology			X												
Allocation				X											
ClinicalHistory	X	X													
Physical exam	X	X					X	X	X	X	X	X	X	X	X
VAS		X					X	X	X	X	X	X	X	X	X
VISA-P		X					X	X	X	X	X	X	X	X	X
blood test													X		
Group MSV BM					X										
Group MSV saline sol.					X										
Group MSV MSV						X									
Group PRP BM sham					X										
Group PRP PRP					X	X									
Bloodbank					X										
MRI		X											X*		X
Ultrasound		X					X	X	X	X	X	X	X	X	X
UTC			X						X		X		X	X	X
DYN			X						X		X		X	X	X
AE					X	X	X	X	X	X	X	X	X	X	X
Medication					X	X	X	X	X	X	X	X	X	X	X

*Elig.* eligibility, *IC* informed consent; *VAS* visual analogue scale; *VISA-P* Victorian Institute of Sport Assessment (Patellar); *BM* bone marrow harvest; MSC Infusion of MSC; *MRI* magnetic Rresonance; *UTC* ultrasound tissue characterisation; *DYN* dynamometry, *PreOp* preoperative study, *AE* Adverse Events.

*X** if the *VAS* and *VISA-P* scales show a significant improvement, and *MRI*, *US*, and UTC provide evidence of healing, the result will be considered positive and the patient will be followed up with confirmation controls at 6 and 12 months. For safety reasons, according to AEMPS criteria, a control test will be performed after the trial, within a period of 2 years after treatment.

If the 6-month evaluation shows negative results, patients may be transferred to the open experimental phase B.

**Table 3 Tab3:** Outcome assessments experimental phase B

Study period															
	Enrollment			Treatment		Follow-up									
Timepoints				0	23 days	1 weeks	2 weeks	3 weeks	6 weeks	8 weeks	10 weeks	3 months	18 weeks	6 months	12 months
IC		X													
Preop + serology			X												
Physicalexam	X	X				X	X	X	X	X	X	X	X	X	X
VAS		X				X	X	X	X	X	X	X	X	X	X
VISA-P		X				X	X	X	X	X	X	X	X	X	X

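### Scheffé contrasts are a poor fit to the stated comparison of MSC with LP-PRP at 3, 6 and 12 months; planned arm contrasts at those months would serve it better at almost no cost

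*Protocol article*

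**What the plan says.** The protocol article states its questions narrowly. The first aim in the Abstract is "to ascertain whether a clinically relevant improvement after 3, 6 and 12 months according to the visual analogue scale (VAS"), together with VISA-P and dynamometry. Main objectives adds the comparator: "To assess the clinical efficacy of MSC injection and compare the results with those obtained in the LP-PRP group".

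The measurement schedule is much denser. Of the follow-up assessments, Response evaluation says: "These will take place at 1, 2, 3, 6, 8 and 10 weeks and 3, 6, 12 months post-treatment". In Table 2, VAS and VISA-P are recorded at baseline and at all nine of these visits (ten assessments). UTC and dynamometry are recorded at baseline, 3 and 8 weeks, and 3, 6 and 12 months (six assessments). MRI is done at baseline, 3 and 12 months (three assessments).

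Under "Inferential statistics tests for comparing groups and time points", the Statistical analysis section plans "ANOVA with repeated measures (or ANCOVA) if covariables with a significant interaction are detected with their corresponding contrast values (Scheffe test"). If normality is rejected it moves to the Mann-Whitney U "test for comparison between groups and Wilcoxon test for comparison between measurements". It adds: "The significance level for all statistical analyses will be 0. 05". It does not say which factor, which visits or which set of contrasts Scheffé applies to.

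**The concern.** Scheffé's method protects every linear contrast that can be formed among the levels of a factor. It suits a search for differences that nobody specified in advance. Here the comparisons of interest are few and known beforehand: the arm difference at three named months. If the factor is visit, or arm by visit, the method charges those three comparisons for all contrasts among the early weeks, about which the aims ask nothing. If the factor is arm alone there is no charge, but the arm effect in a repeated-measures ANOVA is the difference averaged over every visit in the model, which is not the difference at 6 months.

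With 10 patients per arm there is little power to spare. The practical risk is a non-significant Scheffé contrast at 6 months that is read as evidence of no difference between MSC and LP-PRP.

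**Working it through.** **Inputs from the article.** "Twenty patients with a diagnosis of patellar tendinopathy with imaging changes", randomised 1:1, so n = 10 per arm and 18 between-patient degrees of freedom. Significance level 0.05, taken as two-sided. k = 10 assessments for VAS and VISA-P, k = 6 for UTC and dynamometry. The article has no power calculation, SD, assumed arm effect or between-visit correlation, so there is no figure of its own to reproduce.

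**Assumptions.** A true arm difference of 1.3 SD at 3, 6 and 12 months and none before. For scale, this equals the 13-point VISA-P minimum difference in Pain and function if the SD were 10. Three correlation structures: (A) compound symmetry 0.5; (B) 0.3 + 0.7·exp(−weeks/10); (C) 0.3 + 0.7·exp(−weeks/26).

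**Step 1: critical values.** Scheffé: √[(k−1)·F(0.95; k−1, 18(k−1))].
- k = 10 (df 9, 162): 4.18
- k = 6 (df 5, 90): 3.40
- k = 4, baseline plus the three named months (df 3, 54): 2.89
- k = 2, the two arms (df 1, 18): 2.10, identical to t on 18 df
- One planned contrast, t(0.975; 18): 2.10
- Bonferroni over three months, t(1 − 0.05/6; 18): 2.64

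**Step 2: power for the arm difference in change from baseline to 6 months.** Under (A), in SD units, the standard error is √[4(1 − 0.5)/10] = 0.447 and the noncentrality is 1.3/0.447 = 2.91. The noncentral t distribution then gives 11% against 4.18, 32% against 3.40, 61% against 2.64 and 79% against 2.10. Structures (B) and (C) were simulated with 20,000 trials per setting; repeat runs agree to within about one point.

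| Method | A | B | C |
|---|---|---|---|
| Scheffé, ten visits | 11% | 23% | 46% |
| Scheffé, six visits | 32% | 31% | 53% |
| Scheffé, baseline + 3 months | 51% | 41% | 60% |
| Planned, Bonferroni over 3 | 61% | 49% | 68% |
| Planned, unadjusted | 78% | 68% | 83% |

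The loss against Bonferroni is 22 to 50 points with ten visits (68 − 46; 61 − 11), 15 to 29 with six (68 − 53; 61 − 32), and about 7 to 10 with four.

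**Step 3: Scheffé on the arm factor only.** The effect is present at three of ten visits, so the averaged difference is 1.3 × 3/10 = 0.39 SD. Under (A) its standard error is √[(0.5 + 0.5/10) × 2/10] = 0.332, so the noncentrality is 0.39/0.332 = 1.18 and power is about 20%. Across the three structures it is about 15% to 20%. The poor result here comes from dilution over visits and not from Scheffé.

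**Step 4: how far this depends on effect size.** Under (A), 50% power needs 0.93 SD with the unadjusted t and 1.86 SD with ten-visit Scheffé. For a 13-point difference at SD 10 / 15 / 20:
- unadjusted planned contrast: 79% / 45% / 28%
- Bonferroni over three: 61% / 27% / 15%
- ten-visit Scheffé: 11% / 1.5% / 0.4%

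**The case against.** The strongest reply is that the article never ties Scheffé to ten visits. It speaks of groups and time points, and the contrast family is the kind of detail a condensed article may leave to the full protocol. If only baseline and the three named months enter, Scheffé costs 7 to 10 points; with just three levels its critical value (2.55) is below Bonferroni's 2.64. Scheffé is also a valid, conservative method. The omnibus arm-by-visit F test would be significant in about 97% or more of trials in the ten-visit scenario. The Mann-Whitney route has no Scheffé step, and the Discussion already concedes low power.

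Much of this stands. It makes the ten-visit figures conditional and means that the plan contains no proven error. It does not remove the point. An omnibus F test shows that the arm profiles differ somewhere, but not in which month or by how much. The two-arm reading tests a diluted average. Acknowledged low power is a reason not to spend it on contrasts that no aim mentions.

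A reader might also infer that a real 6-month difference will usually be missed because of Scheffé. The article does not support that. It depends on a ten-visit family and on an effect size that is not given; the six-visit figure reaches 53%, and below about 0.93 SD a plain t test fails more often than not as well. Another tempting inference is that the omnibus F test is too liberal for want of a sphericity correction. The article does not say that the correction will be omitted, so that is not part of this point.

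**Conclusion.** The point holds as an inexpensive improvement to the analysis wording. Scheffé is named without a contrast family, and no reading of it serves the stated question as well as planned contrasts do. Across the Table 2 visits it raises the critical value from 2.10 (or 2.64 with a three-month adjustment) to 3.40 or 4.18. Restricted to the named months the loss is modest; restricted to the two arms there is no penalty, but the 6-month difference is not what is tested.

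The power figures rest on the assumed 1.3 SD effect starting at month 3 and on the assumed correlations. For ten visits, the choice of Scheffé is decisive only for true differences of roughly 0.9 to 1.9 SD. Below that range the sample size is the limiting factor; above it, even ten-visit Scheffé detects the difference more often than not. The figures do not apply to MRI, which has three assessments, or to the non-parametric route.

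**What to change.** In the Statistical analysis section, replace the reference to the Scheffé test with pre-planned MSC minus LP-PRP contrasts at 3, 6 and 12 months. Test each with its own error term, for example a two-sample t test on change from baseline or the arm term of a separate ANCOVA for each month. Adjust by Holm over the three months for each outcome, and report every arm difference with its 95% confidence interval. For MRI, only 3 and 12 months are available in Table 2. Report the early-week comparisons descriptively. Holm rejects whenever Bonferroni does, so the Bonferroni power figures are a lower bound for this plan.

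The cost is one sentence and no new data. What is given up is formal error control for unplanned contrasts at the early weeks. The intervals at the named months would also be useful for planning the larger trial that the article foresees.

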### Trial design

#### Study population

Twenty male recreational athletes with a patellar tendinopathy who meet the inclusion and exclusion criteria will be recruited and will be followed for 1 year (Fig. 1).

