Patients will be randomized by the Clinical Research Organization (CRO) (Adknoma) using SAS statistical software (version 9. 4) into either the MSC group or PRP group in a 1: 1 ratio. After randomization, either MSC or LP-PRP will be injected intralesionally and around the affected area of the patellar tendon. To keep patients and evaluating physicians blind to treatment, sham procedures will be performed in both groups (i.e. the MSC group will have blood extracted and will have their tendon injected with normal saline at the first stage of treatment, and the LP-PRP group will undergo a sham bone marrow harvesting at the first stage of treatment). The treating physicians will not be blind to the treatment administered.

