### Pain and function

Pain will be recorded on the VAS, and function will be evaluated by measuring extension forces in the knee using a manual dynamometer.

The pain and functional evaluation will be performed using the VISA-P score, which specifically evaluates pain and function in patellar tendinopathy. The scale ranges from 0 to 100, where a value of 100 indicates the absence of pain at rest, when walking, when climbing up or downstairs or during exercise [50]. VISA-P score values for patients with chronic patellar tendinopathy usually range from 30 to 50. Physical activity may be undertaken again if values are above 60. Patients with score values over 70 are considered fit for competition, although demands are higher for professional athletes. The minimum significant difference has been set at 13 points.

The following VISA-P criteria are used to assess improvement in this trial [51]:
Desired: ≥ 60/100 (after 3 months)Very satisfactory: ≥ 70/100 (after 6 months)Ideal: ≥ 80/100 (after 12 months)

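### Covariate adjustment depends on a significant interaction, and the choice of test on a normality check; at 10 per arm both rules are weak and cost precision that a pre-specified baseline-adjusted model would keep

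*Protocol article*

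**What the plan says.** The rule is in the Statistical analysis section of the protocol article, in the item on "Inferential statistics tests for comparing groups and time points". The parametric branch is "ANOVA with repeated measures (or ANCOVA) if covariables with a significant interaction are detected". The other branch is "or non-parametric tests if the assumption of normality is rejected", namely "Mann-Whitney *U* test for comparison between groups and Wilcoxon test for comparison between measurements". The error rate is common to all: "The significance level for all statistical analyses will be 0. 05".

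The section names no covariate, does not name baseline as one, and does not say what the covariate must interact with. It names no normality test. No other section fixes the covariates or the test in advance.

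The trial has "Twenty male recreational athletes with a patellar tendinopathy", randomised "into either the MSC group or PRP group in a 1: 1 ratio", so 10 per arm. Table 2 schedules VAS, VISA-P, UTC and DYN before treatment, so a baseline value exists for each.

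**The concern.** I read the condition as attached to ANCOVA: repeated-measures ANOVA is the default, and a covariate enters only if an interaction is significant. That selects on the wrong property. Adjustment gains precision when the covariate predicts the outcome, whether or not it interacts with anything. If the interaction meant is covariate-by-group, the rule brings in a common-slope ANCOVA when the slopes look non-parallel, and withholds it when they look parallel and the model is valid.

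The normality rule adds a second data-driven choice. Neither of the rank tests carries a covariate, and they do not estimate a mean difference. Two outcomes, or two visits of one outcome, could be reported on different scales because of a preliminary test on 10 values per arm.

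The Patient and public involvement section says this pilot is to enable a larger RCT. That makes a stable, precise effect estimate for each outcome one of its most useful products.

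**Working it through.** The article gives no power calculation, SD or baseline correlation, so there is no figure to reproduce. The check asks how often each rule would act at this sample size, and what adjustment is worth.

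**Inputs from the article:** 20 patients, 1:1, so n = 10 per arm; alpha 0.05; a VISA-P difference of 13 points (Pain and function: "The minimum significant difference has been set at 13 points").

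**Assumptions:** two-sided tests; normal outcomes with equal variance; baseline-to-follow-up correlation ρ = 0.3, 0.5 or 0.7; an effect of 1 SD, and separately 13 points with SD 12 to 20; interaction read as covariate-by-group; Shapiro-Wilk as the normality test.

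**Step 1: the interaction rule.** Model: follow-up = group + baseline + group × baseline, with ANCOVA used only if the last term has p < 0.05 (6,000 simulated trials per setting).
- Parallel slopes: significant in 4–5% of trials, as the test level implies. ANCOVA is withheld in about 95%.
- True slope difference of 0.5 (SD per SD): significant in 19–20%.
- Type I error of the whole two-stage rule: 0.044 to 0.053.

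**Step 2: the normality rule.**
- If both arms are truly normal, the chance that at least one is rejected is 1 − 0.95² ≈ 0.10; simulation gives 9–10%.
- With 10 values, lognormal skew (σ = 0.5) is detected in 25% of samples and exponential skew in 46%.

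**Step 3: what adjustment is worth.** If baseline is a level of the repeated factor, the group-by-time contrast at one visit is a comparison of change scores, with variance factor 2(1 − ρ). ANCOVA has factor 1 − ρ². The ratio is (1 − ρ²) / [2(1 − ρ)] = (1 + ρ)/2, which is below 1 for any ρ < 1.

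| ρ | Change: 2(1 − ρ) | ANCOVA: 1 − ρ² | Ratio | Power, written rule | Power, ANCOVA always |
|---|---|---|---|---|---|
| 0.3 | 1.40 | 0.91 | 0.65 | 42% | 56% |
| 0.5 | 1.00 | 0.75 | 0.75 | 56% | 65% |
| 0.7 | 0.60 | 0.51 | 0.85 | 78% | 81% |

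The power columns are simulated for a 1-SD effect with 10 per arm and parallel slopes. Repeat runs moved them by no more than about 2 points.

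**Step 4: the same on the VISA-P scale.** With SD 15, 13 points is 13/15 = 0.87 SD. Simulated power at ρ = 0.3/0.5/0.7:
- written rule, baseline as a repeated level: 35/46/66%
- written rule, follow-up values only: 45/46/46%
- ANCOVA always: 46/54/70%

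Over SD 12 to 20 at ρ = 0.5, the normal approximation gives ANCOVA 80% down to 39%, against 68% down to 31% without a covariate. At n = 10 this approximation runs somewhat high (61% against 54% simulated for ANCOVA at SD 15), so the gaps matter more than the levels.

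**The case against.** **The text does not name the interaction partner.** A reader might infer that ANCOVA is used exactly when its assumption fails. That needs the interaction to be covariate-by-group. A covariate-by-time interaction would not breach the parallel-slopes assumption, and in a condensed sentence the word may even be loose for association with the outcome. This objection stands, so the stronger statement is not supported. Under the first two readings the criterion is still the wrong one. Under the third it would still be a data-driven choice of covariates, and the ambiguity itself needs removing.

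**Baseline need not be thrown away.** A reader might infer that the plan ignores baseline. But the tests compare time points as well as groups, repeated-measures ANOVA is named first, the UTC section assesses changes in percentage points, and the Ultrasonography section looks for gap reduction. Baseline may therefore act as a level of the time factor. This also stands, and it shrinks the loss to about 3 points of power at ρ = 0.7. The loss is 14 points at ρ = 0.3.

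**No inflated error rate is shown.** A reader might expect two-stage testing to raise type I error. In these simulations the interaction rule does not.

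**The rank test need not be as weak as it can be made to look.** Mann-Whitney on raw follow-up values has about 51% power for a 1-SD effect at ρ = 0.7, but the article does not say what is ranked; on change scores it is about 74%.

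**This is a small pilot that admits its limited power, and an analysis plan may say more.** Both are true. But the article does not stay silent here: it states the two rules. An analysis plan that follows them inherits the problem, and one that departs from them contradicts the article.

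**Conclusion.** The point holds in a limited form. The article ties covariate adjustment to a significant interaction and the test to a normality check. The first is the wrong criterion, and neither check is informative at 10 per arm: baseline would be left out as a covariate in about 95% of trials with parallel slopes, a slope difference of 0.5 would be missed in about 80%, and moderate skew would usually pass unnoticed.

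The cost is lost precision, about 14, 9 and 3 percentage points of power at ρ = 0.3, 0.5 and 0.7 for a 1-SD effect, and an effect measure that can switch between a mean difference and a rank comparison across outcomes. The documents do not support a claim of inflated type I error, of baseline being discarded, or of ANCOVA being reserved for cases where it is invalid.

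The sizes rest on assumed SDs, correlations and effects, on normal data, and on the covariate-by-group reading. ANCOVA is ahead of the written rule at every correlation tried, though by little when the correlation is high. This should be changed, but it does not invalidate the trial.

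**What to change.** Amend the Statistical analysis text, and any analysis plan, before unblinded analysis:

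- For every continuous efficacy outcome, fix one model in advance with the baseline value of that outcome as covariate. Use either ANCOVA at the stated 3-, 6- and 12-month time points at which the outcome is measured, or a repeated-measures model of the post-baseline visits with baseline as covariate.
- Fit it whatever an interaction or normality test shows.
- Report the adjusted mean difference between groups with its 95% confidence interval.
- Keep interaction tests, with the partner named, and a rank-based or permutation analysis that also adjusts for baseline, as sensitivity analyses for all these outcomes.

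The cost is one degree of freedom: for a two-group comparison at one visit, the residual falls from 20 − 2 = 18 to 20 − 3 = 17. No new data are needed, because Table 2 already schedules the baseline measurements.
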